### Study population

The ForaC study aims to include patients who qualify for decompression of ≤2 cervical neuroforamina by a posterior or an anterior approach because of spondylotic foraminal stenosis with radiculopathy. The target population consists of patients with symptomatic spondylotic foraminal stenosis without central canal stenosis who failed adequate conservative or interventional therapy administered for a minimum of six weeks. Radiculopathy is defined as pain, paralysis or paresthesia in a specific nerve root distribution at C5, C6 or C7. To recruit a rather homogeneous patient population, patients with less severe symptomatology (Neck Disability Index <30 points out of 100) are excluded. Additionally, a radiologically (computed tomography and magnetic resonance imaging) determined pathology at treatment level needs to correlate with the primary symptoms. To minimize risk factors for an unfavourable outcome, patients with significant comorbidities need to be excluded, as this may mask a difference in treatment efficacy. Inclusion and exclusion criteria are outlined in more detail in Table 2.

**Table 2 Tab2:** **Inclusion and exclusion criteria**

Inclusion criteria	Age between 18 and 80 years
	Cervical spondylotic foraminal stenosis causing radiculopathy of C5, C6, or C7 and requiring decompression of ≤2 neuroforaminae
	Radiculopathy is defined as pain, paralysis or paresthesia in corresponding nerve root distribution areas of C5, C6, or C7, and must include at least arm or shoulder pain with minimum of 30 mm on a 100 mm visual analog scale
	Neck Disability Index score ≥30 out of 100
	Unresponsive to non-operative treatment for six weeks or presence of progressive symptoms or signs of nerve root compression in the face of conservative treatment
	Spondylotic foraminal stenosis (determined by magnetic resonance imaging and computed tomography) at treatment level correlating to primary symptoms
	Appropriate candidate for treatment using either of:
	● Anterior approach via ventral discectomy and fusion
	● Posterior approach via foraminotomy, as described by Frykholm
	Psychosocially, mentally, and physically able to fully comply with this protocol, including adhering to scheduled visits, treatment plan, completing forms, and other study procedures
	Personally signed and dated informed consent document prior to any study-related procedures, indicating that the patient has been informed of all pertinent aspects of the trial
Clinical exclusion criteria	Previous cervical spinal surgery at index level
	Lumbar or thoracic spinal disease to the extent that surgical consideration is probable or anticipated within 6 month after the cervical surgical treatment
	Upper extremity degenerative joint diseases (that is, shoulder) to the extent that:
	● Surgical consideration is likely or anticipated within 6 month after the cervical surgical treatment
	● Resulting pain is chronic (>3 month)
	Axial neck pain in the absence of other symptoms of radiculopathy justifying the need for surgical intervention
	Myelopathy
	Neoplasia as the source of symptoms
	Fixed or permanent neurological deficit unrelated to the cervical disc disease
	Disease or conditions that preclude accurate clinical evaluation (for example, neuromuscular disorders)
	Active or chronic infection, systemic or local
	Systemic disease, including HIV, AIDS, or hepatitis
	Active malignancy defined as a history of any invasive malignancy, except non-melanoma skin cancer, unless the patient has been treated with curative intent and there have been no clinical signs or symptoms of the malignancy for a minimum of 5 years
	Paget’s disease, osteomalacia, or any other metabolic bone disease
	Autoimmune disorder that impacts the musculoskeletal system (that is, lupus, rheumatoid arthritis, or ankylosing spondylitis)
	Acute episode or major mental illness (psychosis, major affective disorder or schizophrenia)
	Physical symptoms without a diagnosable medical condition to account for the symptoms, which might indicate symptoms of psychological rather than physical origin
	Recent or current history of substance abuse (drugs, alcohol, narcotics, recreational drugs)
	Anticipated long-term use of systemic steroid medications postoperatively
Radiological exclusion criteria	Symptomatic spondylotic foraminal stenosis, considered for surgical intervention, with contralateral asymptomatic spondylotic foraminal stenosis at the same level with equal or higher extent, as shown by computed tomography
	Cervical disc herniation or central canal stenosis causing radiculopathy or clinical myelopathy
	Myelopathy, as shown by magnetic resonance imaging
	Marked cervical instability on flexion or extension radiographs defined as:
	● Translation >3 mm or
	● Angulation >20°
	Kyphotic segmental angulation >11° at treatment or adjacent levels
	VARIA
	Patient is currently pursuing personal litigation related to spinal diseases
	Prisoner or ward of the state
	Patient has used another investigational drug or device within the 30 days prior to surgery

Informed consent is obtained from each participant.

### Timetable

The timetable and visit plan is outlined in Table 3.

**Table 3 Tab3:** **Visit plan**

	Pre-operation	Intra-operation	Post-operation, 3 days	Discharge	3 months (±2 weeks)	6 months (±1 month)	12 months (±2 months)	24 months (±2 months)	36 and 48 months (±2 months)	60 months (±2 months)
Informed consent	×	-	-	-	-	-	-	-	-	-
Pre-operative history	×	-	-	-	-	-	-	-	-	-
Randomization	×	-	-	-	-	-	-	-	-	-
American Society of Anesthesiologists grade	×	-	-	-	-	-	-	-	-	-
Operative detail	-	×	-	-	-	-	-	-	-	-
Clinical evaluation: neurological status, pain medication consumption	×	-	×	-	×	×	×	×	×	×
Patient self-assessment: Neck Disability Index, Core Outcome Measures Index, Short Form-12 (SF-12) questionnaire	×	-	×	-	×	×	×	×	×	×
Quantitative sensory testing	×	-	-	-	-	×	×	-	-	-
Schedule of radiographic studies										
Neutral, lateral and anterior-posterior	×	×	-	-	×	×	×	×	-	-
Flexion or extension	×	-	-	-	×	×	×	×	-	×
Computed tomography	×	-	×	-	-	-	-	-	-	-
Magnetic resonance imaging	×	-	-	-	×	-	-	×	-	×
Economic data collection										
Hospitalization costs	-	-	-	×	-	-	-	-	-	-
Post-hospitalization costs	-	-	-	-	×	×	×	×	×	×

### Investigational groups

#### Posterior foraminotomy

A midline skin incision is made extending across the cervical motion segments of interest. The neck muscles are subperiosteally dissected from the bone to expose the lamina and a retractor system is applied. Once the facet joint complex is exposed, a Kerrison punch is used to remove some of the medial superior and inferior lamina to access the spinal canal. A microscope is used for improved illumination and visualization. A high-speed drill is then used to thin the medial facet, centred over the joint. The remaining bone overlying the nerve root is removed using angled curettes and small Kerrison instruments. The nerve hook is passed laterally out through the foramen to confirm adequate neural decompression [4, 21].

#### Anterior foraminotomy

A transverse skin incision of 3 to 4 cm is made over the cervical motion segments of interest. Access to the cervical column is prepared by sharp and blunt dissection, opening the superficial fascia at the medial border of the sternocleidomastoid. Under distraction of the target level, a discectomy is performed with full exposure of the posterior longitudinal ligament. Adjacent vertebral osteophytes are then resected with complete foraminotomy on the affected side, with use of the operating microscope. Direct visualization of the involved nerve root from the axillae up to 3 mm distally is obtained. The distraction is released, locking the intervertebral cage firmly into position. A ventral locking plate is used for additional stability, if deemed necessary [14].

#### Randomization

The allocation ratio is 1:1. The randomization code will be generated independently from the clinical investigators according to a random permuted blocks method with varying block size. Randomization will be stratified according to study centres. Statistical Software Stata 10.0 module Ralloc version 3.5.2 (Statacorp College Station, TX, USA) will be used to generate the random code. An independent statistician at the Department of Medical Statistics, Informatics and Health Economics, Innsbruck Medical University will administer the randomization code (Figure 1).

**Figure 1 Fig1:**
[figure not shown]
**Data management and randomization process.** Study data generation at the study sites is clearly separated from data storage, processing and statistical analysis.

#### Data management

Study data generation at the study sites is clearly separated from data storage, processing and statistical analysis in the Department of Medical Statistics, Informatics and Health Economics (Figure 1). This requires a validated database system programmed in a customized software package, which is provided by the Department of Medical Statistics, Informatics and Health Economics of the Medical University, Innsbruck. The system includes an audit trail facility and will be used to define the database structure, data entry, for handling data cleaning processes, and for final data storage. Data evaluation takes place by double entry of the data and manual and visual evaluation of plausibility. After entry of all collected data and clarification of all queries, the database will be closed at the completion of the study. This performance has to be documented.

#### Sample size and power calculation

The sample size calculation is based on the primary endpoint of the study, the group difference in the Neck Disability Index. A reduction in Neck Disability Index score of 14 to 17 points out of 100 is considered to be clinically meaningful [22, 23]. Thus, 14 points were used as the required difference between groups applicable for the power calculations. Moreover, a group standard deviation of 20 is assumed, based on results of comparable previous trials [24, 25]. A sample size calculation was performed based on a two-group *t* test (GraphPad StatMate Software, version 2.0); 35 patients per group are required to detect a 14-point difference with 80% power on a two-sided level of significance of 0.05. A loss to follow-up of less than 20% was considered adequate for final calculation of sample size. Accordingly, the proposed sample size amounts to 88 patients, that is, 44 patients in each group. In case of non-normality of the Neck Disability Index, this sample size is also sufficient to detect a difference of 14 points with a Mann-Whitney *U* test.

#### Statistical analysis

Endpoints will be analyzed as appropriate depending on data distribution with a two-sided 0.05 level of significance. Detailed descriptive statistics will be provided for the data collected and 95% confidence intervals will be calculated for all relevant estimates. Clinical follow-up data will be analyzed by analysis of covariance (ANCOVA) or generalized model alternatives for categorical or semiquantitative data. Changes within the treatment groups over time as well differences between groups will be assessed simultaneously. The primary analysis will follow the intention-to-treat principle. All randomized patients with a complete preliminary examination will be considered for inclusion into the intention-to-treat population. Further sensitivity analysis will be provided to evaluate robustness of the results with regard to unexpected circumstances (for example, impact of ‘cross-over’ patients who are not treated as randomized but are required to be analyzed as randomized (intention-to-treat principle) and centre effects. Secondary endpoints will be analyzed in an exploratory manner at a two-sided significance level of 5%. Safety and tolerability parameters will be analyzed descriptively. Frequencies will be compared by Chi-square or Fisher’s exact tests, as appropriate. Analysis of time-dependent probabilities of critical events will be performed using the Kaplan-Meier method. Furthermore, multivariate event analyses will be performed using Cox proportional hazard regression models. The last-observation-carried-forward approach will be employed, in order to perform an intention-to-treat analysis of the primary efficacy endpoint in consideration of all randomized patients. In addition, for the purpose of a supportive sensitivity analysis, multiple imputation procedures will be applied. Statistical analysis will be performed 12, 24, 36 and 60 months after completion of the last visit of the study population at the specified time points.

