## Methods/design

### Study design

The ForaC study is a multicenter randomized, controlled, parallel group superiority trial with 88 adult patients allocated to the groups in a 1:1 ratio. The expected enrolment time is 2 years, and the conclusion of the study is estimated at 7 years. The primary study endpoint is the difference in Neck Disability Index between treatment groups at five years after intervention. As one of the secondary study endpoints, the Core Outcome Measures Index is applied to assess pain, back-specific function, work disability, social disability and patient satisfaction. Moreover, changes in physical and mental health are assessed by the Short Form-12 (SF-12) questionnaire, version 2. Adjacent level degeneration, segmental lordosis and overall cervical sagittal alignment are determined by flexion or extension X-rays and magnetic resonance imaging. Pre-operative American Society of Anesthesiologists grade staging might allow the identification of risk factors. Neurological status and the quality and quantity of current pain medication are documented. Operation time and time of hospitalization are documented. Quantitative sensory testing is performed to assess and quantify sensory nerve function non-invasively. We also evaluate the direct costs of hospital care and the indirect costs of follow-up treatment outside the hospital. Costs of surgery and hospitalization, including duration of inpatient treatment, cost of nursing, costs of medication and physiotherapy, are assessed after discharge from the hospital according to internal cost-estimate lists from the hospital operator. In addition, the indirect costs following discharge from hospital (for example, including physiotherapy, rehabilitation centres, pain medication, medical consulting) are documented on a routing sheet. Each study participant will receive such a routing sheet when leaving the hospital, with instructions for documentation. Postoperative care is not standardized in the study protocol and is to be performed according to the standard of care for spondylotic foraminal stenosis surgery at the participating sites. An external orthosis is not used in either group. Primary and secondary outcome parameters are outlined in more detail in Table 1. Ethics approval was attained at the local research ethics committee of the Medical University Innsbruck (UN4702). This study complies with the World Medical Association Declaration of Helsinki Ethical Principles for Medical Research Involving Human Subjects, 2008.

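### Randomisation is stratified by centre, but the article gives centre a role only in the sensitivity analyses and nowhere states it as a term in the primary ANCOVA

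*Protocol article*

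**What the plan says.** In the protocol article, the Randomization section sets a 1:1 allocation by a "random permuted blocks method with varying block size" and adds: "Randomization will be stratified according to study centres".

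The Study design section defines the primary comparison: "The primary study endpoint is the difference in Neck Disability Index between treatment groups at five years after intervention".

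The Statistical analysis section names the method: "Clinical follow-up data will be analyzed by analysis of covariance (ANCOVA) or generalized model alternatives for categorical or semiquantitative data". It lists no covariates. Centre is mentioned once in that section, in the sentence that begins "Further sensitivity analysis will be provided to evaluate robustness of the results with regard to unexpected circumstances" and ends, after the example of cross-over patients, with "required to be analyzed as randomized (intention-to-treat principle) and centre effects".

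No other part of the article gives centre a role in the analysis. The Study design section leaves postoperative care to the standard of each participating site. Trial status reports two Austrian sites at the start, two German sites to follow, and possibly more.

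**The concern.** Blocking within centre balances the arms within each centre, so differences between centres largely cancel out of the treatment contrast. A model without centre still counts those differences as residual variation. Its standard error then describes a noisier design than the one used: the interval is too wide and the p-value too large whenever centres differ in outcome. Centre is also known from the first patient, so it sits oddly among checks for the unforeseen.

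At stake is some precision in the one confirmatory comparison, at five years, planned on 35 evaluable patients per arm. It should also be settled in advance which result is primary if the analyses with and without centre fall on opposite sides of 0.05.

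**Working it through.** **Inputs from the Sample size and power calculation section.** Difference 14 NDI points, SD 20, two-sided 0.05, 80% power, 35 per group, loss to follow-up 20%, 44 per group (88 in total).

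**Reproducing the plan's figure.** Normal approximation: n = 2(1.96 + 0.8416)² × 20² / 14² = 2 × 7.849 × 400 / 196 = 32.04, rounded up to 33 per arm. The exact *t*-test solution is 33.02. The stated 35 is close to both and slightly generous; *t*-test power at 35 per arm is 82.3%. With 20% loss, 35 / 0.8 = 43.75, so 44 per arm and 88 in total. The stated size reproduces.

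**Assumptions for the centre question.** The documents give no centre ICC, so 0 to 0.20 is used. Block sizes of 2, 4 and 6 are assumed. There are 2 or 4 centres of equal expected size, 70 evaluable patients and a total SD of 20. Each setting has 6,000 simulated trials, analysed by a linear model without and then with centre as a fixed effect. Monte Carlo error is about 0.3 points for type I error and 0.5 for power.

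| Centres | ICC | Type I error, without / with centre | Power, without / with | CI half-width (NDI points), without / with | Ratio of half-widths |
|---|---|---|---|---|---|
| 4 | 0 | 5.0% / 5.0% | 82.6% / 82.4% | 9.51 / 9.52 | 1.00 |
| 4 | 0.05 | 4.9% / 5.2% | 82.8% / 83.5% | 9.47 / 9.31 | 1.02 |
| 4 | 0.10 | 4.3% / 5.2% | 84.5% / 86.0% | 9.39 / 9.05 | 1.04 |
| 4 | 0.20 | 3.4% / 4.8% | 86.6% / 89.9% | 9.25 / 8.52 | 1.09 |
| 2 | 0.10 | 4.4% / 4.8% | 84.4% / 85.6% | 9.27 / 9.02 | 1.03 |
| 2 | 0.20 | 3.9% / 4.9% | 87.6% / 90.0% | 8.99 / 8.49 | 1.06 |

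Power rises with the ICC in both columns because total SD is held at 20, so a larger centre share leaves less variation within centres. The comparison that matters is within each row.

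**Hand check of the widths.** With K centres of equal size, the model without centre has an expected residual variance of about σ²[(1 − ρ) + ρ(K − 1)/K]. The variance that drives the treatment contrast is about σ²(1 − ρ). The ratio of interval widths is therefore √{[(1 − ρ) + ρ(K − 1)/K] / (1 − ρ)}. For K = 4:

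- ρ = 0.05: √(0.9875 / 0.95) = 1.02
- ρ = 0.10: √(0.975 / 0.90) = 1.04
- ρ = 0.20: √(0.95 / 0.80) = 1.09

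These agree with the simulated ratios.

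**Power lost by omitting centre, four centres.** 83.5 − 82.8 = 0.7, 86.0 − 84.5 = 1.5 and 89.9 − 86.6 = 3.3 points at ICC 0.05, 0.10 and 0.20.

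**The case against.** The strongest reply is that the article never excludes centre from the ANCOVA. It lists no covariates at all, and a covariate list is ordinary SAP content. The term for centre effects is undefined and could mean a treatment-by-centre interaction, which belongs in a sensitivity analysis anyway. The sentence has an unclosed bracket, so it is not even clear whether centre is an example of an unexpected circumstance or a separate item.

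Much of this stands. A reader might infer that the primary confidence interval and p-value are known not to match the design. The documents do not support that, because the primary model's terms are not given. Silence on covariates alone would be no finding. What remains is that the article does assign the stratification factor a role, and the only one it assigns lies outside the primary model. If a fuller document already includes centre, the article's wording misleads and is worth correcting.

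Other inferences also go too far:

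- **A false-positive risk.** The error runs the other way; without centre, simulated type I error did not exceed 5%.
- **An underpowered trial.** Power without centre stays above the planned 80% in every setting simulated.
- **A wrong sample size.** Sizing on a two-group *t* test and analysing by ANCOVA is ordinary practice.
- **A larger loss of level.** The closed form 2[1 − Φ(1.96/√(1 − c))] gives 4.4% and 3.9% for centre shares c of 5% and 10%. It takes that share as realised exactly and the balance as perfect; the simulation with four centres gives 4.9% and 4.3%.
- **A further gain from baseline NDI.** Baseline is the usual covariate in the ANCOVA already named, so its benefit is no measure of what omitting centre costs.
- **Surgeon preference and skill as evidence of centre effects.** The Background and Discussion remarks concern how treatment is chosen in routine practice; here the approach is randomised. The support for centre differences is the site-specific postoperative care.

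**Conclusion.** The point holds as a modest improvement to the stated plan. The factor used to stratify the randomisation should be a declared term in the primary model, and the article mentions it only among the sensitivity analyses.

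The consequence is conditional: it arises only if centre is in fact omitted and is prognostic. Under the assumed ICC of 0.05 to 0.20 with four centres and 70 evaluable patients, type I error is about 4.9% to 3.4%, the interval about 2% to 9% wider, and about 1 to 3 points of power are lost. At the lower end, the departure of type I error from 5% is within Monte Carlo error. With two centres the effect is smaller, and at ICC 0 adjusting costs essentially nothing. The simulation treats the 70 evaluable patients as the randomised set; dropout would loosen the balance within centres somewhat and so weaken the conservatism.

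**What to change.** State the primary analysis in one sentence: ANCOVA of 60-month NDI with treatment, baseline NDI and study centre as terms. Because more sites may join, add a rule for pooling very small centres, set before the data are seen. Define the centre-effects sensitivity analysis as the treatment-by-centre interaction.

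The cost is a change of wording. Baseline NDI and centre are already recorded, no patients or procedures are added, and the sample size of 88 stands.

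### The five-year Neck Disability Index comparison rests on last observation carried forward, which can bias the primary estimate and misstate its precision; multiple imputation or a repeated-measures model should be primary instead

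*Protocol article*

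**What the plan says.** The Study design section fixes the endpoint: "The primary study endpoint is the difference in Neck Disability Index between treatment groups at five years after intervention". The Statistical analysis section then assigns the missing-data method: "The last-observation-carried-forward approach will be employed, in order to perform an intention-to-treat analysis of the primary efficacy endpoint". The alternative has a lesser role: "for the purpose of a supportive sensitivity analysis, multiple imputation procedures will be applied".

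Table 3 (visit plan) has a row for "Patient self-assessment: Neck Disability Index, Core Outcome Measures Index, Short Form-12 (SF-12) questionnaire". It is marked pre-operatively, at 3 days, and at 3, 6, 12, 24, 36, 48 and 60 months. Nothing in the article limits how far back a value may be carried. Entry to the analysis population needs no post-operative score: "All randomized patients with a complete preliminary examination will be considered for inclusion into the intention-to-treat population". The wording therefore does not exclude even the pre-operative score.

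On expected loss, the Sample size section says: "A loss to follow-up of less than 20% was considered adequate for final calculation of sample size".

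**The concern.** Carrying the last score forward assumes that a patient's NDI stays where it was at the last visit. A patient last seen on day 3 would enter the five-year comparison with an early postoperative score; one last seen at 12 months would enter with a score four years old.

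The Background section makes a changing difference between the approaches plausible. It cites adjacent segment disease at 2.9% per year after anterior fusion against 0.7% after posterior foraminotomy. It raises possible same-level degeneration and kyphosis after the posterior approach. It also cites one disc-herniation study with a short-term neurological advantage for the anterior approach. If the difference does change, carried-forward values mix earlier differences into the 60-month contrast.

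There is also a question of precision. A single filled-in value is treated as a measured one, so the confidence interval ignores that up to a fifth of the five-year scores were never seen. Both problems fall on the trial's one confirmatory result.

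**Working it through.** **Inputs from the protocol.** Difference 14 points, SD 20, two-sided 0.05, power 80%, 35 per group before and 44 per group after allowing for 20% loss (Sample size section); NDI visits from Table 3.

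**The plan's own figure.** The article states "35 patients per group are required to detect a 14-point difference with 80% power on a two-sided level of significance of 0.05".
- Normal approximation: 2 × [20 × (1.960 + 0.842) / 14]² = 32.04, so 33 per group. The t test gives 33.02, so 34.
- The stated 35 is close, and has t-test power of 82.3%.
- 35 / 0.80 = 43.75, so 44 per group and 88 in total, as stated.
- 20% of 44 is 8.8, so about 9 five-year scores per arm could be carried forward.

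**Formula, equal dropout.** If a fraction d drops out at random in each arm, the expected carry-forward difference is (1 − d) × D60 + d × Dlast. D60 is the true 60-month difference and Dlast the average difference at the carried visits. With d = 0.20 and D60 = 14:

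| Dlast (assumed) | Expected estimate | Bias |
|---|---|---|
| 14 | 14.0 | 0 |
| 7 | 12.6 | −1.4 |
| 0 | 11.2 | −2.8 |
| −7 | 9.8 | −4.2 |

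If D60 = 0 and Dlast = 7, the estimate is a spurious +1.4.

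**Linear build-up.** Assume the difference grows in proportion to time, reaches 14 at 60 months, and last visits are spread evenly over day 3 (0.1 month) and 3, 6, 12, 24, 36 and 48 months.
- Mean last-visit time: (0.1 + 3 + 6 + 12 + 24 + 36 + 48) / 7 = 18.44 months.
- Dlast = 14 × 18.44 / 60 = 4.30.
- Expected estimate: 0.8 × 14 + 0.2 × 4.30 = 12.06.

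Simulations with 44 per arm, SD 20, inter-visit correlation 0.6 and random 20% dropout gave 11.9 to 12.1 points with 77% to 79% power. Observed cases gave 13.9 to 14.1 points with 81% to 84% power. Imputation using all visits recovered about 14.0 points.

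**Unequal dropout, no true difference.** The bias is (dA − dB) × c, where c is the average shared change from the last visit to 60 months.
- Assume mean NDI of 45, 35, 30, 27, 25, 25 and 25 at the seven earlier visits and 25 at 60 months. Then c = (20 + 10 + 5 + 2) / 7 = 5.29.
- 30% against 10% dropout: 0.20 × 5.29 = 1.06 points.
- 35% against 5%: 0.30 × 5.29 = 1.59 points.
- With c = 10, 30% against 10% gives 2.0 points.

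Simulated values ran from 0.6 to 2.0 points depending on the recovery assumed, with type I error of about 5% to 7%.

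**Precision.** Without baseline adjustment, the standard error is 20 × √(2/44) = 4.26 if all 88 scores count as observed, against 20 × √(2/35) = 4.78 for 35 observed per arm. Carry-forward would report an error about 11% smaller (4.26 / 4.78 = 0.89). That gain is earned only if earlier differences equal the 60-month one. With no difference at any visit and 20% random dropout in both arms, simulated type I error stayed at 5.2%.

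**The case against.** **Bias is conditional.** A reader might infer that carry-forward necessarily biases this trial, or always pulls the result toward zero. The document supports neither. With a constant 14-point difference and equal random dropout, the simulated estimate was 14.0. An early difference that later fades pushes the estimate away from zero. This objection stands.

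**Late divergence is not the stated rationale.** A reader might take the five-year endpoint to have been chosen to capture late effects. The article gives no reason for five years. It words the adjacent-segment risk as a possibility and calls same-level degeneration controversial. The two late mechanisms count against opposite arms and could partly cancel. This stands too.

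**The 14-point build-up is generous.** Rates of 2.9% and 0.7% per year differ by 2.2 × 5 = 11 percentage points at five years. If each extra case scored 20 to 50 NDI points worse (an assumption), the mean difference would be 2.2 to 5.5 points. The linear case loses (14 − 12.06) / 14 = 14%, which on that scale is about 0.3 to 0.8 points. The 2-point loss is therefore an illustration, not a forecast.

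**Few day-3 scores would be carried.** Spread evenly over seven last visits, 8.8 / 7 gives about 1.3 patients per arm. The analysis plan, not shown here, may also restrict which scores qualify. So the weight lies on carry-forward as a whole.

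**Imbalance is assumed.** Nothing in the document predicts unequal loss, and 30% or 35% in one arm exceeds the planned 20%, although these pairs average 20%.

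**Multiple imputation is already planned.** A reader would see any disagreement. But the article does not say which result prevails, so the carry-forward result remains primary. The general statement that changes over time and group differences are assessed together does not displace the specific assignment for the primary endpoint.

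**Conclusion.** The point holds in conditional form. The protocol positively chooses carry-forward for its primary five-year comparison; this is not a detail left open. The method is unbiased only if the between-group difference is constant and dropout is equal and unrelated to outcome, and the protocol's background gives reason to doubt the first condition.

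Under the stated assumptions the size is moderate: about 2 points off a late-building 14-point difference, power a few percentage points below an observed-case analysis, and a spurious 1 to 2 points under marked imbalance (less if recovery is flatter). Trajectories, correlation and dropout patterns are assumptions. Outcome-dependent dropout was not simulated. Neither a fixed direction of bias nor serious type I error inflation can be claimed from the document. This should be fixed, but it does not invalidate the design.

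**What to change.** Reverse the order of the methods in the Statistical analysis section. Make one of these primary:
- a likelihood-based repeated-measures model of all scheduled NDI scores from 3 to 60 months, with treatment, visit, treatment-by-visit, baseline NDI and centre, reading the treatment contrast at 60 months; or
- the multiple imputation already planned, done by arm and using all visits.

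Keep carry-forward, if at all, as a sensitivity analysis, and do not carry the day-3 or pre-operative score to 60 months. Date the change before the 60-month data are analysed.

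The cost is one paragraph and a little more modelling work; no new patients, visits or data are needed. The confidence interval may be wider. With seven visits an unstructured covariance has 7 × 8 / 2 = 28 parameters for 88 patients, so a simpler fallback should be named. Both options assume that the observed scores explain the missingness, so they reduce the problem of outcome-dependent dropout without removing it.
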